### Participant recruitment

Participant recruitment will be conducted within primary care services, at individual participating GP surgeries. Up to 50 older people with mild to moderate frailty will be recruited in line with previous sample size recommendations for feasibility studies.^43^ Eligibility criteria for older adults with mild to moderate frailty to participate in the study are outlined in box 1. The clinical care team from participating GP surgeries will identify eligible participants through existing medical records.

Box 1Inclusion and exclusion criteriaInclusion criteriaAged ≥65 years.Scoring as mild or moderately frail using the Electronic Frailty Index.Diagnosis of one or more long-term conditions including chronic obstructive pulmonary disease, type 2 diabetes, heart disease or asthma.Living in their own homes.Capacity to consent to participate.Able to communicate fluently enough in English to take part in the study.Able to recall their experiences sufficiently to engage with a health coach.Self-reported ability to use digital technology independently or with support.Exclusion criteriaNursing home resident or on the active waiting list for a place.Individuals who have a terminal illness and are being managed for end-of-life needs.Lacking the capacity to consent (eg, advanced dementia).

Three strategies will be used to recruit patients (1) via text message invitation to eligible patients which provides a link to a website with further information about the study, participant information sheet and contact information for the research team. Potential participants will be followed up by the research team to provide an opportunity to answer questions, confirm eligibility and obtain informed consent to participate, (2) by a member of the research team approaching eligible participants at the GP surgery, signposted by the clinical team and (3) via leaflets provided to eligible patients by the clinical team.

### Digital support for patients

Patients with low digital literacy will be supported by the research team to access the digital HC and mobile health platforms. They will be offered a training manual, developed by the research team and coproduced alongside the SEG and PPI group alongside digital support leaflets and guidance on keeping safe online. To reduce the risk of digital inequity, internet-enabled tablets may be provided to individuals who lack a device, for the length of the study. Internet and data packages (via local council schemes) will be provided if the participant lacks access to an established internet connection. Digital support will be offered throughout the study via local council services (volunteer digital upskilling clinics embedded within public spaces, eg, GP surgeries and council libraries) and the research team.

### Outcome measures

#### Primary outcomes

The primary outcome measures are the feasibility and acceptability of the DIALOR intervention. Feasibility will be determined from the number of health coaches trained, the number of participants recruited, retention and adherence to the intervention as well as any adverse events. To determine the acceptability of the intervention and to explore barriers and enablers to the implementation of the intervention, semistructured interviews will be conducted with patients with mild to moderate frailty (and their carers where appropriate) (n=20), HCPs and health coaches (n=20) who participated in the study.

The interviews will consist of open-ended questions to explore participant views of the intervention, barriers and facilitators to inform the design of further studies. To understand the factors influencing implementation, the interview schedule will be underpinned by NPT.^44^ NPT is an implementation theory providing a framework to identify and explain important elements of the implementation process. As such, it informs an understanding of the social processes through which new or practice can be implemented, embedded and integrated into care settings.

#### Secondary outcomes

The secondary outcomes will include the measurement of functioning, quality of life, physical activity levels, frailty severity, diet quality and engagement using validated outcome measures.

Physical functioning, a key outcome in frailty trials,^45^ will be measured using the Modified Barthel Index (MBI)^46^ and Lawton-Brody Instrumental Activities of Daily Living (IADL).^47^ The MBI will measure older adults’ functional ability using 10 items, with a higher score reflecting the higher ability to function independently. The MBI has been found to be of reasonable reliability when used among older adults.^48^ The IADL will measure more complex activities of daily living using eight key domains. The International Physical Activity Questionnaire short form (IPAQ-SF) will measure older adults’ activity levels in the last 7 days.^49^ The evidence supporting the IPAQ-SF as an indicator of relative or absolute physical activity is weak.^50^ However, it is a validated generalised outcome measure for older adult populations (65 years or over).^51^

Quality of life is a core outcome in frailty trials^52^ and will be measured using the EuroQol-5 Dimensions-5 Levels (EQ-5D-5L) questionnaire, which includes five health areas (mobility, self-care, usual activities, pain/discomfort and anxiety/depression). These five health areas are assessed with five main response levels (no problems, slight, moderate, severe or unable), along with a Visual Analogue Scale.^53^

Frailty severity will be measured using the Groningen Frailty Indicator (GFI).^54^ The GFI is a multidimensional screening instrument consisting of 15 self-report items. It is a feasible and widely used screening instrument for identifying frail older adults.^55 56^ Higher GFI scores indicate higher frailty levels and an increased need for integrated care.^57^

The Short Form Food Frequency Questionnaire (SFFFQ) will measure dietary quality. The SFFQ asks about foods which respondents might have consumed, on average, over a set time period (3 months) and is found to be an effective instrument for assessing diet quality in large-scale studies with UK adult populations.^58^

Social engagement will be measured using the Lubben Social Network Scale (LSNS-6) and mental well-being will be measured using the Warwick-Edinburgh Mental Well-Being Scale (WEMWBS).

Self-reported indicators such as height, weight, body mass index, number of falls (per year), goal attainment, alcohol intake and smoking habits (if applicable) will be measured at baseline (preintervention), throughout the study during digital HC intervention and at 6 months (postintervention).

Data will be collected from the mobile health platform which will be recorded automatically by inbuilt tracking software, including usage patterns from the number of logins, and the length of time that older people and their carers use the platform. These data will be collected at 6 months for each patient participant (postintervention).

### Data analysis

#### Quantitative data analysis

Data will be entered into a secure database for analyses. Statistical analyses will be conducted using statistical software SPSS (V.28.0). Descriptive statistics: median (IQR); mean (SD); number (%) and CI—will be used to analyse the number of volunteers recruited and retained, as well as participants’ adherence to the intervention and pre–post intervention outcome measures to assess the feasibility of delivering the intervention. Preanalyses and postanalyses at 6 months will be conducted to determine if the intervention had an impact on the lifestyle management of frailty measured by functioning (MBI, IADL), social engagement (LSNS-6), mental well-being (WEMWBS) quality of life (EQ-5D-5L), physical activity (IPAQ-SF), frailty indicator (GFI), diet quality (SFFFQ) and self-reported indicators.

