**Methods and analysis:**

This is a non-randomised feasibility, single-group, pretest/post-test study, using qualitative and quantitative methods. The digital health coaching intervention (DIALOR—DIgitAL cOaching for fRailty) has been developed for implementation to older adults, aged 65 years or older with mild to moderate frailty and diagnosis of one or more long-term health conditions in the community. Participants will receive 12 weeks of health coaching and have access to a mobile health platform for 6 months. The primary outcome measure is the acceptability and feasibility of DIALOR along with a range of secondary outcome measures (including frailty, functioning measures, quality of life, social engagement, diet quality and self-reported indicators) collected at baseline and at 6 months. The findings will inform whether a wider effectiveness trial is feasible and if so, how it should be designed.

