**Ethics and dissemination:**

Ethical approval has been granted by the Southeast Scotland Research Ethics Committee 02 (reference: 22/SS/0064). Research findings will be disseminated in a range of different ways to engage different audiences, including publishing in open-access peer-reviewed journals, conference presentations, social media, dissemination workshop with patients, carers, and healthcare professionals and on institution websites.

STRENGTHS AND LIMITATIONS OF THIS STUDYA strength of the study design is using a mixed-methods approach with a qualitative understanding of the implementation process and quantitative measures to assess the effects on health outcomes and whether the trial is feasible.There is strong involvement of stakeholders and people with the lived experience to develop and guide the study.Potential limitations are as a feasibility study, it will assess a pretest and post-test intervention with non-randomisation of sample and to sufficiently engage hard-to-reach target groups including those with poor digital literacy and low socioeconomic status, impacting representation of the participant group and generalisability of the findings.

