**Figure 1 F1:**
[figure not shown]
Overview of the DIALOR intervention and its functionalities. CARE, Congratulate, Ask, Reassure, Encourage; COPD, chronic obstructive pulmonary disease; DIALOR, DIgitAL cOaching for fRailty; LTC, long-term condition.

The primary objectives of this study are as follows:

Explore barriers and facilitators of the digital intervention from the perspectives of health coaches and healthcare professionals (HCPs) and determine the essential and desirable features of the intervention (wants and needs; preferred outcomes) to identify what functions will be most useful for the target population.Explore how HC can provide support for the management of mild to moderate frailty and LTCs from the perspectives of older people with mild to moderate frailty, carers, HCPs and health coaches.Determine the acceptability and feasibility of the intervention for older adults with mild/moderate frailty and another LTC referred to access HC services and willing to engage with the mobile health platform.

The secondary objectives of this study are as follows:

Explore the factors which inhibit or facilitate implementation including contextual factors, recruitment processes, resources needed, potential mechanisms and pathways to impact.Explore the acceptability and suitability of outcome measures (to inform sample size estimation and determine the primary outcome measure) for a future randomised controlled trial of the intervention (should it be feasible).Measure key domains for secondary outcome measures including participants who are able to self-report measures.

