### Study design

This feasibility study is a non-randomised, single-group, pretest/post-test study, using qualitative and quantitative methods. This protocol was developed in accordance with the Standard Protocol Items: Recommendations for Intervention Trials reporting guidelines.^40^

This will be a mixed-methods prospective cohort study conducted within primary care settings in Southwest England. First, online group training on the intervention will be provided for health coaches by the research team, with top-up training and support as necessary throughout. A training manual will also incorporate frailty awareness and the Congratulate, Ask, Reassure, Encourage model approach.^41 42^ Intervention delivery will be tailored to each patient, with goals and strategies to help achieve them developed in conjunction with the health coach.

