### Status

The trial commenced in September 2023 and is expected to be completed by September 2024.

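### The 6-month pre-post analysis is given a causal purpose that a single-group study cannot serve, and the study calendar largely confounds pre/post with autumn-winter versus spring-summer

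*Protocol article*

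**What the plan says.** The Study design section is unambiguous: "This feasibility study is a non-randomised, single-group, pretest/post-test study, using qualitative and quantitative methods". Up to 50 people are to be recruited (Participant recruitment), with outcomes at baseline and 6 months (Abstract).

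The Quantitative data analysis section then gives two purposes for the same data. It first lists descriptive statistics and confidence intervals for recruitment, retention, adherence and "pre–post intervention outcome measures to assess the feasibility of delivering the intervention". The next sentence says "Preanalyses and postanalyses at 6 months will be conducted to determine if the intervention had an impact on the lifestyle management of frailty", and names eight instruments (MBI, IADL, LSNS-6, WEMWBS, EQ-5D-5L, IPAQ-SF, GFI, SFFFQ) plus the self-reported indicators.

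The strengths and limitations box counts as a strength the use of "quantitative measures to assess the effects on health outcomes and whether the trial is feasible". It also lists the non-randomised pretest/post-test design as a limitation, but the consequences it draws are for representation and generalisability.

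The objectives at the end of the Introduction are more modest. For these outcomes the objective is "Measure key domains for secondary outcome measures including participants who are able to self-report measures". The abstract says of the study as a whole: "The findings will inform whether a wider effectiveness trial is feasible and if so, how it should be designed". On timing, the Status section says: "The trial commenced in September 2023 and is expected to be completed by September 2024".

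**The concern.** Determining whether an intervention had an impact needs some account of what would have happened without it. This design provides none. Whatever the 6-month change turns out to be, it combines any intervention effect with the natural course of frailty, regression to the mean, care received alongside, reporting by participants who know they are being coached, and time of year. No later choice of statistical method supplies the missing comparator, so this is not a detail that an unseen analysis plan could settle.

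If the sentence is followed as written, the report will draw a causal conclusion about secondary outcomes that the data cannot carry. The conclusion would appear in a study whose findings are meant to inform whether and how a larger trial is run. The calendar makes one of the alternative explanations concrete, because season moves largely in step with the pre/post contrast.

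**Working it through.** The protocol states no power, alpha, effect size or SD, so there is no figure of its own to reproduce. The check has three parts.

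**1. The stated purposes side by side**

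| Place | Purpose given to the pre-post outcome data |
|---|---|
| Introduction, secondary objectives | Measure key domains; explore acceptability and suitability of outcome measures |
| Abstract | Inform whether an effectiveness trial is feasible and how to design it |
| Quantitative data analysis, first statement | Assess feasibility of delivery |
| Quantitative data analysis, second statement | Determine whether the intervention had an impact |
| Strengths box | Assess effects on health outcomes, and trial feasibility |

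The first three agree. The last two claim effects, which no stated objective calls for.

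**2. Calendar**

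Inputs: September 2023 to September 2024 (Status) and 6-month follow-up (Abstract). Assumptions: the start is first enrolment, the end is last follow-up, and enrolment is uniform over the feasible window.

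- Latest baseline = 30 September 2024 minus 6 months = 30 March 2024.
- Baselines: 1 September 2023 to 30 March 2024, 212 days. Follow-ups: 1 March to 30 September 2024. The windows overlap only in March 2024.
- Baselines in October to March: 182/212 = 86%. The same 86% of follow-ups fall in April to September.
- December-February baseline with June-August follow-up: 91/212 = 43%. September-November baseline with March-May follow-up: 91/212 = 43%. The remaining 30/212 = 14% have a March baseline and a September follow-up.

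Sensitivity to the window:

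| Enrolment window | Baseline Oct-Mar (= follow-up Apr-Sep) | Winter to summer | Autumn to spring |
|---|---|---|---|
| 1 Sep 2023 to 30 Mar 2024 | 86% | 43% | 43% |
| 1 Sep 2023 to 29 Feb 2024 | 84% | 50% | 50% |
| 30 Sep 2023 to 1 Mar 2024 | 99% | 59% | 40% |
| 1 Sep to 30 Nov 2023 | 67% | 0% | 100% |

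Exposure differs by instrument, because recall windows differ (Secondary outcomes):

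- IPAQ-SF covers the last 7 days, so it follows the assessment date closely.
- SFFFQ covers 3 months. Someone enrolled before about 7 November (67/212, about a third) reports mainly summer and early-autumn diet at baseline and winter diet at follow-up, so the seasonal direction reverses.
- Falls are counted per year and span all seasons.

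**3. How easily a non-intervention shift could look like an effect (illustration)**

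Suppose the intervention does nothing and there is a background drift of d, in units of the SD of within-person change. The probability that a two-sided 95% CI for the mean change excludes zero is, by normal approximation,

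P = Φ(d√n − 1.96) + Φ(−d√n − 1.96).

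For n = 50, √n = 7.07:

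- d = 0.2: Φ(1.414 − 1.96) + Φ(−1.414 − 1.96) = 0.293.
- d = 0.3: Φ(2.121 − 1.96) + Φ(−2.121 − 1.96) = 0.564.

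| d (assumed) | n = 50 | n = 40 | n = 35 |
|---|---|---|---|
| 0 | 5% | 5% | 5% |
| 0.1 | 11% | 10% | 9% |
| 0.2 | 29% | 24% | 22% |
| 0.3 | 56% | 48% | 43% |
| 0.5 | 94% | 89% | 84% |

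The values of d are assumptions; the protocol gives no figure for drift from any source. The CI half-width is 1.96/√50 = 0.28 SD of change at n = 50.

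**The case against.** The best defence is that one loose clause is being read against an otherwise cautious document. Feasibility and acceptability are the primary outcomes, effectiveness is left to a later trial, the non-randomised design is listed as a limitation, and the analysis section names only descriptive statistics and CIs. Retention is itself a feasibility measure, so drop-out will be visible. All of this is true, and it confines the problem to the secondary outcomes. It does not remove it. The impact sentence follows the descriptive one and gives the analyses a different purpose. The listed limitation does not say that change cannot be attributed, and the same box presents assessing effects as a strength.

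The objection does stand against several stronger readings that a reader might be tempted to make:

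- *That pre/post is virtually winter versus summer.* Strict winter-to-summer pairs are 43% to 59% over the longer windows tried, and none if everyone enrols by November. Only the half-year contrast is supported, and only if the stated start is first enrolment. No recruitment window is given. Counting the 9-month development period from September 2023 would put first enrolment at June 2024 and its follow-up at December 2024, past the stated end, so first enrolment is the more natural reading.
- *That every outcome is seasonally biased in the same direction.* Falls are not affected in this way, diet may reverse in early enrollees, and the protocol gives no information on the seasonality of the well-being or social network scales.
- *That false-positive rates from significance testing are built into the plan.* Eight independent 5% tests would give 1 − 0.95⁸ = 34% for at least one false positive, but no hypothesis test or alpha is named.
- *That the observed change will set the future trial's effect size or pick its primary outcome.* The protocol ties the work meant "to inform sample size estimation and determine the primary outcome measure" to acceptability and suitability of the measures. It nowhere says that the observed change will be the target difference.

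**Conclusion.** The concern holds for the stated purpose of the analysis. The protocol commits the 6-month pre-post comparison to a causal conclusion that a single-group design cannot deliver, goes beyond its own objectives in doing so, and does not withdraw the claim elsewhere. This part needs no assumption.

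The seasonal part is conditional. If the study began enrolling in September 2023 and the last follow-up is in September 2024, pre/post is largely confounded with autumn-winter versus spring-summer (86% of baselines and of follow-ups under uniform enrolment over the full window; 67% to 99% over the windows tried). It bears most directly on IPAQ-SF. The 29% to 56% figure shows sensitivity to an assumed drift of 0.2 to 0.3 SD of change at n = 50; it is not an estimate of the drift in this study.

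The primary outcomes and the sample size are untouched, and the protocol states no decision rule that rests on these secondary outcomes. The point is still worth acting on, because following the text would produce an unsupported conclusion and a wording change prevents it.

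**What to change.** In Quantitative data analysis, replace the impact sentence with:

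> Within-participant change from baseline to 6 months will be described (mean or median, with 95% CI) to inform outcome choice and variability estimates for a future trial, and will not be attributed to the intervention; dates of assessment will be reported and season noted as a limitation.

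Keep the list of instruments and self-reported indicators after it. Reword the strengths statement to match, so that the quantitative measures describe change in health outcomes and inform feasibility and no longer claim to assess effects.

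The cost is wording in two places and reporting of assessment dates. Sample size, visits and instruments stay as they are. The study gives up an impact claim that it could not have supported.

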#### Qualitative data analysis

Data collected from all the interviews and focus groups will be transcribed verbatim and analysed using thematic analysis (TA). TA is a commonly used method for identifying, analysing and reporting patterns or themes within data.^59^ There are six key phases: phase 1—familiarisation with the data, phase 2—initial code generation, phase 3—searching for and generating themes, phase 4—reviewing themes, phase 5—defining and naming themes and phase 6—producing the report. Analysis of qualitative data will be conducted using Microsoft Word, and or alternative software such as NVivo (V.12). RC will analyse codes using NPT^44^ and the BCTT^37^ to focus on the social processes shaping the implementation process from making sense of the intervention to engaging in it (individually and collectively) and embedding this (normalising) in everyday practice (or people’s everyday lives) and to identify the facilitators and barriers present throughout the implementation process. Themes will be developed, from the codes, to reflect the lived experience and views of patient participants, health coaches and HCPs regarding the digital HC and mobile health platform intervention. MS will code 25% of interviews and focus groups separately to develop, discuss and agree on themes with RC. Finally, members of the core research team ([name], MB, CC and JM) will be consulted to develop, discuss and agree on themes via an iterative process.

